### Recruitment

Each school involved in the ACT OUT! trial will be chosen based on its receptiveness and interest in participating in the project. Only schools that have provided a signed letter of agreement from an authorized official will be allowed to participate in the study. This study will utilize a waiver of parental consent (opt out), which was approved as part of the IRB submission. Neither the intervention nor the questionnaire poses more than minimal risk to participants or anyone else secondarily connected with the study (eg, their families and teachers). Surveys will be grouped by classroom and administered in a confidential manner. As part of this protocol, a notification letter and copy of the complete posttest survey instrument will be sent home to parents a minimum of 2 weeks before initial subject interaction (parent letter included as Multimedia Appendix 1). Parents and/or guardians will be able to opt their child out of the study simply by returning the second page of the letter to the school. Students will be provided with a brief summary of the study at the top of each survey form. They will be informed that they may also opt out of the study by simply not completing the instrument or by selectively skipping items based on comfort level.

The practical purpose of using a waiver of parental consent in recruitment is the substantial difference in participation prevalence as well as potential ethical concerns resulting from the probable exclusion of underrepresented minorities and high-risk populations, as in the study by White et al [43]. Indeed, several recent studies have suggested that active parental consent and opt-in methods produce smaller student samples with different characteristics, including some related to this study (such as bullying) [43-45]. These issues mirror similar findings related to sociodemographics, risk behaviors, and study participation reported in the previous several decades of school-based research [46-49]. In general, these studies imply that active parental consent may reduce sample size, introduce bias, and thus limit the generalizability of studies with youth.

### Assignment of Interventions

#### Allocation Sequence Generation

This trial is a cluster randomized trial; for each pair of classrooms (eg, 2 seventh-grade classrooms at the same school), a computerized random number generator will assign the classrooms to intervention (0) or control (1).

#### Allocation Concealment

The opt-out process will occur before the assignment. Allocation sequence will be concealed to the member of the research team who will assign each classroom to either the intervention or control group, until the moment of assignment.

#### Allocation Implementation

Allocation sequence generation will be completed by the research team, and data will be provided to participating schools after consent/assent has been finalized.

### Blinding

Due to the nature of the ACT OUT! trial, blinding of the trial participants, school officials, and members of Claude McNeal Productions is not possible. Furthermore, as data management will occur via the primary research team, group identity cannot realistically be masked. However, we have included 2 statistical/methodological consultants in the project team who will be asked to verify all analyses using masked group assignment.

### Participant Timeline

Recruitment for the study will begin in the fall of 2019, and interventions are expected to conclude in December 2019. A visual participant timeline is included in Figure 2.

### Data Collection Methods

#### Survey Collection Procedures

Each classroom will be assigned a random cluster ID with fixed leading values for grade level and arm (eg, 4C-12345678). Each classroom will be given a study packet that contains the appropriate number of survey and response forms, a manila envelope, a white envelope, and an administrator checklist, the latter of which is available as Multimedia Appendix 2. All survey forms and manila envelopes will also be imprinted with the appropriate cluster ID.

A classroom teacher will oversee survey administration after reviewing the administrator checklist. The voluntary and confidential nature of the survey will repeatedly be emphasized per the checklist. The administrator will record the number of individuals present in the classroom on the manila envelope (serving as a denominator for the cluster response rate). Absence for the 2-week postsurvey will not prevent a participant from completing the 6-month postsurvey. All surveys distributed to students will be placed by students into the manila envelope upon completion, even if left blank, which will allow calculation of the numerator of the cluster response rate. Survey forms that were never handed out at all (*extras*) will be placed into the white envelope by the administrator.

#### Quality Control

Data will be collected using a form designed in Scantron Design Expert and scanned directly into a database using an Insight 700c scanner (Scantron) to avoid data entry errors associated with manual transcription.

Intervention fidelity will be recorded at each instance by an employee of Claude McNeal Productions who is not a member of the ACT OUT! ensemble. This individual will use a form generated by the researchers that documents congruence between the observed performance and a checklist of planned elements (element present/element absent). To establish reliability, a second individual from Prevention Insights will attend 15% (6/40) of performances and complete fidelity checklists to compute interrater reliability (free-marginal kappa). The checklist will be published as a multimedia appendix to the study results.

#### Retention

To increase individual-level participation in the study, researchers will utilize an assent procedure approved by the appropriate IRB. As noted previously, this procedure, as opposed to active parental consent, is appropriate when the risks associated with the study are minimal. Participants may, however, withdraw from the study for any reason at any time, either via parental or participant request.

As hypotheses will be tested at 2 points in time, individuals who drop out of the study after providing data at the first posttest will not be excluded from hypothesis testing for proximal (2-week) outcomes.

#### Data Matching

To facilitate confidentiality, researchers will need to establish longitudinal linkages between surveys without collecting identifying information. This presents a risk of potential data loss. Meta-analytic research published within several months of trial protocol development asserts that there is no currently accepted best-practice standard for how to accomplish this most effectively in a way that preserves confidentiality and maximizes accurate matching of data between waves of collection [50]. However, these researchers found numerous benefits to accomplishing this goal using self-generated identification codes (SGICs) versus alternate methods, including true anonymity, improved response quality, utility, and maximal compliance with regulatory requirements. Researchers have also noted that SGICs are more effective when applied within smaller units or clusters [51], as is the case here.

The primary disadvantage of using an SGIC is that participants must accurately remember and report the same information [50]. The most common protocol used in longitudinal matching has been to use a combination of gender, race, and various snippets of personal information that are theoretically memorable (eg, middle initial, birth month, and mother’s initial), as in the study by Kearney et al [52]. However, although such a method is generally a secure way of matching surveys without identifying individual participants, it may cause concern among parents or youth [53].

For this protocol, we opted to generate an SGIC using procedures drawn from computer science and informatics literature related to password security questions. These questions are used by both children and adults to retrieve lost passwords and are intended to be both secure and memorable [54], meeting the needs of the SGIC as identified in the survey research literature. In Rabkin’s review [54] of security questions from banking institutions, questions designated as *weak* included those that are inapplicable to large segments of the target population (eg, a question about spouses), those that are not memorable (eg, last name of kindergarten teacher), and those that are ambiguous (eg, multiple truthful answers are possible, or a response is not static, such as *favorite food*) [54]. Later research on this topic also found that memorability of responses is greater for personal questions than for numbers and that memorability for all items declines over time, although high-success questions will experience minimal decline in successful recall, even after a year [55].

Using this evidence, the project will generate an SGIC with the following elements:

Classroom IDGenderRaceEthnicity“How many *older* brothers and sisters do you have?” (0, 1, 2, 3 or more)“What color is your *backpack*? (if it is several colors, what color is it *mostly*?; black, red, green, blue, brown, purple, pink, a different color, I do not have a backpack)“What was the name of your *first pet*? (If you have never had a pet before, write the word “None” here;*handwritten entry*)Seventh and 10th grades only “What are the last two digits in your school locker combination? (for example, if your combination is 5-13-27, you would put 27)” (*digit entry*, I do not have a lock)

Computerized matching will occur within cluster ID. First, direct matches will be identified, and then 1-off matches (eg, all questions similar but 1) will be identified per well-established recommendations [50]. Any multiple matches (eg, more than 2 posttests matching a pretest SGIC) will be partitioned along with nonmatched data for manual inspection. Importantly, the *first pet* question includes handwritten entry, and so obvious similarities in handwriting can be used as a secondary matching tool.

### Analytic Methods

#### General Issues

Missing data may result from nonresponse to specific items or attrition following the baseline survey (eg, dropout following pretest but before any other analyses), and the type of missingness will be analyzed. Potential types include missing completely at random (MCAR; missingness is not related to the scores of any measured variable), missing at random (MAR; missingness is related to values of other measured variables, but not to the scores of that variable itself), or missing not at random (MNAR; missingness is related to scores of that variable itself). Data that are MCAR and MAR will be managed using multiple imputation [56]. As we expect some uncertainty in matching students across time points, each baseline survey will be considered a primary key, and surveys at postintervention will only be matched with each students’ baseline survey if researchers are reasonably certain that the ID code is a match from prespecified criteria. Surveys from postintervention that cannot be matched will not be included in the analysis. Students missing postintervention surveys will be considered missing due to attrition, and they will be included in the multiple imputation analysis as intention to treat.

Sensitivity analyses will be performed for plausible cases of data MNAR to examine the consistency of results across models. If the results are consistent, we will conclude that the conclusions are not compromised. We will also evaluate all appropriate statistical assumptions, such as outliers, variance heterogeneity, specification error, and nonnormality, before analysis.

#### Statistical Analysis

The intervention arm (ACT OUT! participation) will be compared against the control arm (TAU) in testing the primary hypotheses using an intention-to-treat model. This means that all individuals who are randomized will be included in the main analyses. As shown in Table 1, linear mixed models (LMM) or generalized LMM will be used to test all hypotheses. Baseline values will be included as covariates in each LMM, and all outcome values except receptivity and school-level data (truancy, absenteeism, and referrals to discipline for bullying) will be captured at baseline. Both fixed and random effects will be evaluated.

**Table 1 table1:** Hypotheses, measures, and methods of analysis.

Outcome type and hypothesis		Time frame	Outcome measure	Method of analysis
**Primary**				
	Intervention improves short-term SEC^a^; long-term SEC	2-week follow-up; 6-month follow-up	DSECS-S^b^ (continuous)	LMM^c^; GLMM^d^ if nonnormal data
	Intervention reduces incidence of bullying others	2-week follow-up; 6-month follow-up	Thomas et al [36] 13-item bullying others scale (continuous)	LMM; GLMM if nonnormal data
	Intervention reduces incidence of being bullied	2-week follow-up; 6-month follow-up	Thomas et al [36] 13-item bullying scale (continuous)	LMM; GLMM if nonnormal data
	Intervention reduces incidence of referrals to discipline for bullying	6-month follow-up	Objective count data (continuous)	GLMM
**Secondary**				
	Intervention improves social awareness (seventh and 10th grades only)	2-week follow-up; 6-month follow-up	WCSD^e^ social-emotional competency assessment (continuous)	LMM; GLMM if nonnormal data
	Intervention improves emotion regulation (seventh and 10th grades only)	2-week follow-up; 6-month follow-up	WCSD social-emotional competency assessment (continuous)	LMM; GLMM if nonnormal data
	Intervention improves relationship skills (seventh and 10th grades only)	2-week follow-up; 6-month follow-up	WCSD social-emotional competency assessment (continuous)	LMM; GLMM if nonormal data
	Intervention improves responsible decision making (seventh and 10th grades only)	2-week follow-up; 6-month follow-up	WCSD social-emotional competency assessment (continuous)	LMM; GLMM if nonnormal data
	Receptivity to ACT OUT! will moderate impact of the intervention	2-week follow-up; 6-month follow-up	Dent et al [39] instrument (continuous)	LMM; GLMM if nonnormal data
	Explore outcome differences by grade level (fourth, seventh, and 10th grades)	2-week follow-up; 6-month follow-up	Four outcome measures from primary objectives (all continuous)	LMM; GLMM if nonnormal data
	Intervention will improve truancy and absenteeism	6-month follow-up	Objective count data (continuous)	GLMM
	Intervention will improve academic performance	6-month follow-up	GPA^f^ standardized to a 4.0 scale (continuous)	LMM; GLMM if nonnormal data

^a^SEC: social-emotional competence.

^b^DSECS-S: Delaware Social-Emotional Competency Scale.

^c^LMM: linear mixed model.

^d^GLMM: generalized linear mixed model.

^e^WCSD: Washoe County School District.

^f^GPA: grade point average.

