### Intervention

Eligible classrooms will be randomized to attend a 1-hour ACT OUT! interactive, semi-improvisational psychodrama performance or to continue with their school day as normal (TAU). Interventions will be delivered within the standard school day as defined for each classroom and school. The ACT OUT! production will include 3 vignettes paired with moderated discussions between the audience and the actors, and the latter will remain in character for the duration of the intervention. Intervention guidelines will be made available alongside the published study.

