#### Secondary Outcomes

##### Student Receptivity to the ACT OUT! Intervention

This will be measured at the 2-week posttests using an instrument based on work published by Dent et al [39], which measures the degree to which adolescents find the event to be enjoyable, interesting, a waste of time, boring, understandable, difficult to understand, believable, important, and helpful, each on a 4-point ordinal scale.

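### Receptivity is defined only for students who saw the performance, so the Table 1 hypothesis that it moderates the intervention's impact is not estimable; only a within-arm association is

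*Protocol article*

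**What the plan says.** Table 1 (Secondary) of the protocol article gives the hypothesis "Receptivity to ACT OUT! will moderate impact of the intervention". Its time frame is the 2-week and 6-month follow-ups, its outcome measure is the receptivity instrument, and its method is LMM, or GLMM if the data are nonnormal. The Statistical Analysis section says that "linear mixed models (LMM) or generalized LMM will be used to test all hypotheses".

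Under Student Receptivity to the ACT OUT! Intervention, the instrument is said to capture "the degree to which adolescents find the event to be enjoyable, interesting, a waste of time, boring", together with further ratings of the same kind. On timing, the text reads "This will be measured at the 2-week posttests". The Statistical Analysis section excludes receptivity from baseline collection: the measures taken at baseline are "all outcome values except receptivity and school-level data".

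According to Choice of Comparators and Intervention, control classrooms simply carry on with ordinary school activity. The Limitations section argues that contamination is a minor threat precisely because control students do not experience the performance.

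**The concern.** To say that a variable moderates an intervention's impact is to say that the difference between arms changes with its level. The variable must then have a value in both arms, and ideally one fixed before randomisation. Receptivity meets neither condition. It is a reaction to the performance, so control students have nothing to rate, and it is recorded after randomisation.

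The risk lies in interpretation. A mixed model run on the available ratings will return a slope and a P value. If students who already have higher social-emotional competence (SEC) tend to rate the show more favourably, the slope can be positive with no programme effect at all. Under the printed hypothesis, that slope could be reported as evidence that the programme works better in receptive students.

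The row also does not say whose effect is moderated. It gives the receptivity instrument as the outcome measure, whereas the next row, on grade level, names the four primary outcome measures. Grade is a sound moderator for this design: it is known in both arms before randomisation.

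**Working it through.** The plan states no figure for this analysis, so there is none to reproduce. The check has three steps.

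**1. Can the interaction be estimated?** Take the fixed effects needed for moderation: intercept, arm A (1 = intervention), receptivity R, and A×R. This needs no numerical assumption.

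- If controls are given any constant c for R, then R = c − c·A + A×R. One column is a combination of the others. A numerical check with c = 0 gives rank 3 for 4 columns.
- If controls are dropped for lack of a rating, A equals the intercept and A×R equals R. The rank is 2 for 4 columns.

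In both cases the only receptivity slope the data identify is the one inside the intervention arm.

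**2. How large can that slope be with no programme effect?** The Statistical Analysis section requires the baseline value as a covariate, so the relevant slope is the adjusted one. Let r be the correlation of receptivity with baseline SEC and, equally, with follow-up SEC. Let ρ be the correlation between baseline and follow-up SEC. With standardised variables:

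adjusted slope = r(1 − ρ) / (1 − r²)

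The protocol gives neither r nor ρ. Assuming r = 0.3:

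| ρ (assumed) | Calculation | Slope (SD per SD) |
|---|---|---|
| 0.5 | 0.3 × 0.5 / 0.91 | 0.16 |
| 0.7 | 0.3 × 0.3 / 0.91 | 0.10 |
| 0.8 | 0.3 × 0.2 / 0.91 | 0.07 |

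**3. How often would it look significant?** This was simulated with 40 intervention classrooms of 20 students, 400 runs and no programme effect. Baseline and outcome each shared 70% of their student-level variance with a latent trait, and the outcome had an added classroom effect with SD 0.2. Outcome was regressed on baseline and receptivity with cluster-robust standard errors. All inputs except the classroom numbers are assumptions.

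| Correlation of receptivity with the trait | Mean slope | Significant at 5% |
|---|---|---|
| 0 | 0.00 | 6% |
| 0.2 | 0.05 | 49% |
| 0.4 | 0.11 | 97% |

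The formula agrees. Here r = k√0.7 and ρ = 0.7, where k is the correlation in the first column. For k = 0.2, 0.167 × 0.3 / (1 − 0.028) = 0.05. For k = 0.4, 0.335 × 0.3 / (1 − 0.112) = 0.11.

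The simulation assumes complete follow-up. With the roughly 20% loss the protocol plans for, the percentages in the last two rows would be lower, while the slopes would stay the same if the loss were unrelated to these variables.

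**Timing.** The row covers two follow-ups, and they differ. At 2 weeks the rating and the outcomes come from the same posttest, so either could influence the other. At 6 months the rating precedes the outcome, but it is still a post-randomisation variable that was not assigned at random.

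**The case against.** The strongest reply is that the article prints no arm-by-receptivity term. Table 1 names only a model class, and the statement that the two arms are compared is made for the primary hypotheses. A mixed model of outcome on receptivity within the intervention arm, adjusted for baseline, fits the printed method, and model terms are commonly left to a statistical analysis plan. That is fair as far as the method goes, and the plan should not be described as having specified an inestimable formula. The hypothesis is still stated wrongly, because a within-arm slope is an association and not moderation of impact. No later document can supply receptivity to a performance that control students did not attend.

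Four stronger readings are tempting, and the protocol does not support them.

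- A reader might infer that a correlation of 0.3 creates a spurious 0.3 SD difference, as large as the d = 0.30 the trial is powered for. That ignores the baseline covariate the plan requires; with it, the slope falls to about 0.07 to 0.16 SD.
- A reader might take it as stated that no control student gives a rating. The article does not say which arm completes the items. That controls have no valid value is an inference from their not attending; any answer they gave would be a different variable.
- A reader might suppose that the plan means to impute receptivity for controls. The General Issues section applies imputation to item nonresponse and attrition only.
- A reader might extend the problem to the trial's main conclusions. No primary hypothesis, sample-size input or allocation step depends on this row.

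**Conclusion.** The point stands, limited to one secondary hypothesis. The protocol fixes a moderation hypothesis, a moderator that exists only after exposure, no baseline value, and an unexposed control arm. These cannot be combined into an estimate of moderation. This conclusion rests on the design alone, together with the inference that control students cannot rate a performance they did not see.

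The size of the possible misreading does depend on assumptions. With correlations of 0.2 to 0.4 between receptivity and SEC or an underlying trait, and baseline-to-follow-up correlations of 0.5 to 0.8, the baseline-adjusted slope under no programme effect is roughly 0.05 to 0.16 SD per SD of receptivity. Slopes of 0.05 and 0.11 SD reached significance in about half and nearly all of the simulated trials respectively. If receptivity were unrelated to pre-existing traits, this bias would vanish, but the slope would still not be moderation.

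The point is of moderate weight. Reporting receptivity descriptively, as the secondary outcome it also is, is not affected.

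**What to change.** Reword the Table 1 row as a non-randomised association, within the intervention arm, of receptivity with follow-up SEC and the two bullying scales, adjusted for the baseline value and classroom clustering. Name those outcomes in the row, do not call the result moderation, and interpret the 2-week and 6-month results separately because the order of measurement differs. Discipline referrals should stay out of this student-level analysis, since they are obtained only in aggregate by cluster.

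If effect modification is of real interest, add an exploratory analysis. Predict receptivity from baseline variables in the intervention arm with cross-fitting, assign the predicted score to students in both arms, and test arm by predicted score. This asks whether the effect differs by a student's expected receptivity, which is defined in both arms, and not by the reaction itself.

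The cost is one table row and matching analysis wording, with no new data. The drawback of the exploratory option is low power if baseline variables predict receptivity poorly.
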